### **3.4. Potential risks and adverse events**

#### **3.4.1. Potential risks:**

We consider the risks of this study to be small.

The specific risks are:

Blood Loss: The total blood loss for both parts of the study will be approximately 800 ml. Patients with pre-existing anemia will be excluded and we will consult patients not to donate blood 4-5 months before and after the study. The 4 parts of the study will be spread over 4 months.

Intravenous catheters: Intravenous catheters used during the clamp are associated with a mild to moderate degree of pain upon insertion, and a small risk of localized infection.

Euglycemic clamp: The euglycemic clamp is a safe technique, which has been used by our group for more than 10 years without any side effects. The insulin doses increase plasma insulin levels to concentrations in the range of fasting to low post-prandial concentrations, and will be gradually decreased as soon as the subcutaneously injected insulin detemir will start its effect. The risk of hypoglycemia during the clamp is minimal since 10% glucose is being infused and plasma glucose is monitored every 10-30 min.

#### **3.4.2. Adverse events**

The study investigators will oversee and monitor all aspects of the study including subject consent, study conduct, data handling as well as reporting any adverse events to the local ethical comittee and Swissmedic

#### **3.4.3. Assessment of risk:**

The procedures included in this study are considered to present only mild risk to research participants. However, the study will be reviewed and reported as required by the "Verordnung über klinische Versuche mit Heilmitteln" des Schweizerischen Bundesrates vom 17. Oktober 2001".

#### **3.4.4. Attribution of adverse events:**

Adverse events will be monitored for every subject participating in the study and attributed to the study procedures/design by the study investigators according to the following categories:

Possible: Adverse event(s) may be related to investigational procedure(s)/agent(s) or other intervention.

Unlikely: Adverse event(s) will doubtfully be related to investigational procedure(s)/agent(s) or other intervention.

#### 3.4.5. Plan for grading adverse events:

The following grade levels will be used in defining the severity of adverse events:

Serious: Death, immediate risk of death, hospitalization or a prolongation of existing hospitalization or a persistent or significant disability/incapacity.

Non-serious: Mild or moderate adverse event or within normal limits.

#### 3.4.6. Plan for reporting serious adverse events:

While no serious adverse events are expected, the study investigators will report any serious adverse events to the local ethical committee and Swissmedic within 48 hours.

#### 3.4.7. Plan for reporting non-serious adverse events:

Non-serious unanticipated adverse events will be reported to the local ethical committee and Swissmedic on an annual basis.

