## **6. Significance and outlook**

With the increasing incidence and prevalence of type 2 diabetes mellitus, insulin therapy will be of major importance, because insulin is highly effective. Long-acting insulins like insulin detemir and insulin glargine are being used more and more frequently. Safety data about high doses of insulin are necessary and reassuring for physicians treating obese patients with insulin. As all insulins show a dose-dependent prolongation of their action profile, an examination of the effect of high doses, as often needed in insulin resistant states, is important for the prevention of hyper- and hypoglycaemia and thus for the safety and efficacy of insulin therapy.

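### The adverse event rules give a severe but non-serious event no class, and disagree on whether an anticipated non-serious event such as hypoglycaemia is reported

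*Protocol*

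**What the plan says.** Four parts of Protocol section 3.4 bear on this.

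- **Grading (3.4.5).** The section announces its purpose: "The following grade levels will be used in defining the severity of adverse events". It then gives two levels. The upper one is "Serious: Death, immediate risk of death, hospitalization or a prolongation of existing hospitalization or a persistent or significant disability/incapacity". The lower one is "Non-serious: Mild or moderate adverse event or within normal limits".
- **General duty (3.4.2).** The investigators' oversight covers "study conduct, data handling as well as reporting any adverse events to the local ethical comittee and Swissmedic". Nothing here separates expected from unexpected events.
- **Specific reporting rules (3.4.6 and 3.4.7).** For serious events, "the study investigators will report any serious adverse events to the local ethical committee and Swissmedic within 48 hours". For the rest, "Non-serious unanticipated adverse events will be reported to the local ethical committee and Swissmedic on an annual basis".
- **Named risk (3.4.1).** Hypoglycaemia appears under the clamp procedure and is rated low: "The risk of hypoglycemia during the clamp is minimal since 10% glucose is being infused".

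Sections 3.4.4 and 3.4.8 add that adverse events are monitored and attributed in every subject, and that the investigators review the data weekly. Section 6 gives part of the motivation: "Safety data about high doses of insulin are necessary and reassuring for physicians treating obese patients with insulin".

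**The concern.** Severity (how intense an event is) and seriousness (what outcome it leads to) are different scales. Section 3.4.5 puts both under one label and leaves a hole between them: there is no place for an event that is severe in intensity but leads to none of the listed outcomes. An inpatient clamp can produce such an event. A patient with marked symptoms of low glucose who is corrected while glucose is being infused is already in hospital and may need no longer stay.

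The reporting rules then leave it open whether a non-serious episode goes to the authorities. An investigator who follows 3.4.2 would report it. One who follows the more specific 3.4.7 would not, because the event was foreseen.

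At stake is whether events of the same kind are classified and reported alike across subjects, insulins and doses. Section 6 places the study in the context of high-dose safety and the prevention of hypoglycaemia, so ambiguity about this event matters more than it would for an incidental one.

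**Working it through.** The plan states no figure on this point, so there is nothing to reproduce. The check is to take each kind of event through the sections.

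**Step 1: is hypoglycaemia anticipated?** The protocol does not define *unanticipated*. Section 3.4.1 lists hypoglycaemia among the clamp risks. On the ordinary reading, a risk named in advance is anticipated. This is an inference.

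**Step 2: apply the rules to each kind of event.**

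| Event | Class in 3.4.5 | 3.4.2 | 3.4.6 | 3.4.7 |
|---|---|---|---|---|
| Meets a seriousness criterion | Serious | Reported | Reported within 48 hours | Does not apply |
| Mild or moderate, unanticipated | Non-serious | Reported | Does not apply | Reported annually |
| Mild or moderate, anticipated | Non-serious | Reported | Does not apply | Not covered |
| Severe, meets no seriousness criterion | None | Reported | Does not apply | Undetermined; not covered if treated as non-serious and anticipated |

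The first two rows are consistent. The third shows the conflict between 3.4.2 and 3.4.7. The fourth shows the grading gap and, for an anticipated event, the conflict as well.

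**Step 3: do other sections close the gap?** Section 3.4.4 has all adverse events monitored and attributed, but its two categories concern relatedness and supply no severity level. Section 3.4.8 gives a weekly review but does not say how a severe non-serious event is to be labelled in it. No section says which low glucose reading counts as an adverse event.

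**Step 4: are the data there?** Section 3.3.2 has plasma glucose measured every 10 to 30 minutes, for up to 36 hours after injection. A full-length session therefore gives between 36 × 60 / 30 = 72 and 36 × 60 / 10 = 216 values. Section 3.5.3 speaks of hourly measurement, which would give 36. Sessions that end early give fewer. These are counts of measurements, not of events. They show only that low values during a session would be on record, so a rule for identifying events needs no new sampling.

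**The case against.** The strongest reply is that nothing is lost. Section 3.4.2 already covers every adverse event, 3.4.4 monitors them in every subject, 3.4.8 brings the data to the investigators each week, and the clamp readings record any low value. Section 3.4.7 governs only what goes to the ethics committee and Swissmedic each year; it does not limit what is recorded, reviewed or published. The protocol rates the clamp risk as minimal, and a life-threatening episode, or one that prolongs the stay, is serious and reportable within 48 hours.

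Most of this stands, and it rules out several stronger readings that a reader might infer:

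- *That the trial could appear free of hypoglycaemia at high doses.* This does not follow. The rule in question concerns reports to authorities, and monitoring, review and glucose recording continue regardless.
- *That hypoglycaemia is outside every reporting rule.* It is not, because 3.4.2 has no such limit. The defect is disagreement between two sections, not a clear exclusion.
- *That hypoglycaemia is the main hazard.* The protocol does not say so.
- *That a hypoglycaemia endpoint or a table by insulin and dose is missing.* In a euglycaemic clamp, low values depend largely on the infusion algorithm, and the insulin effect is measured by glucose consumption and duration of action. Tabulation may properly be left to the analysis plan, which is not at hand. Section 6 does not promise comparative hypoglycaemia rates.

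The reply does not reach the grading scale, which is a stated rule with a missing level. Nor does citing 3.4.2 remove the difficulty: it is one side of the contradiction, and the more specific rule says something narrower.

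**Conclusion.** The point holds in two parts. First, 3.4.5 mixes severity with seriousness and leaves a severe event that meets no seriousness criterion without a class. This can be read directly from the text. Second, 3.4.2 and 3.4.7 disagree on whether anticipated non-serious events are reported to the ethics committee and Swissmedic. That hypoglycaemia falls in this group rests on treating a risk named in 3.4.1 as anticipated.

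This is a minor to moderate correction to safety reporting. It affects non-serious episodes only. The number of such episodes cannot be estimated from the document, and no figure in the plan changes. The primary pharmacodynamic comparison does not depend on it.

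**What to change.** 1. In 3.4.5, record two items for each event: seriousness (yes or no, using the existing outcome criteria) and severity (mild, moderate or severe).
2. Reconcile 3.4.2 with 3.4.7 so that hypoglycaemia is explicitly covered, for example by removing the word *unanticipated* from 3.4.7 or by naming hypoglycaemia there.
3. State that low-glucose events are recorded from the glucose values already collected, with the limit set by the investigators, and shown at the weekly review in 3.4.8.

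The cost is a few sentences in sections 3.4.2 to 3.4.8 and a longer annual report. No extra blood sampling is needed.

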#### 3.4.8. Data and safety review and frequency:

The study investigators will review the data and study conduction on a weekly basis and determine whether the study should continue unchanged or whether modifications to the protocol and/or consent form are required.

### **3.5. Data analysis and statistics**

#### 3.5.1. Null-hypothesis for the primary endpoint:

The total glucose consumption and the mean duration of action will not be different between the two insulins and the two insulin dosages.

#### 3.5.2. Null-hypothesis for the secondary endpoint:

With increasing dosage, the mean duration of action of insulin detemir and insulin glargine will not last over 30 hours

The plasma peak insulin levels and the time from the respective peak levels to half max levels at the two dosages of both insulins will not be different.

The total glucose consumption and the duration of action of the insulins is not correlated to the degree of obesity, i.e. of body mass index and of body composition (central fat accumulation) in obese patients with type 2 diabetes mellitus.

Both insulins (glargine and detemir) are dose-equivalent in terms of their glucose-lowering effect in obese patients with type 2 diabetes mellitus.

#### 3.5.3. Measurements and calculations

Performance of an euglycemic hyperinsulinemic clamp by hourly measurement of plasma glucose, insulin and C-peptide and calculation of the area under the curve (AUC) of the necessary glucose infusion rate (GIR) which is necessary to maintain plasma glucose at 5 mmol/l. For serum insulin and serum C-peptide, descriptive statistics for pharmacokinetic measures are performed (maximal serum insulin concentration [Cmax], time to Cmax [tmax], and AUC; minimal serum C-peptide concentration [Cmin], time to Cmin [tmin] and AUC).

End of insulin action is defined as the time at which plasma glucose consistently increases to > 8.3 mmol/l despite adaptation of glucose infusion.

Since it is debated, that a given unit of insulin detemir is equipotent to a given unit of insulin glargine, we compare the activity ratio (standardized activity ratio) of the two insulins by the total glucose consumption (g glucose/U of insulin administered). This activity ratio will be used to determine further pharmacodynamic effects like the peak of action, the time from peak to half maximal action and the total duration of action.

We will perform a mixed model with a random subject effect in order to calculate differences between the two different dosages and the different insulins (total glucose consumption, duration of action). Among others, covariates that will be assessed include BMI, age, sex.

As there are several primary endpoints, a Bonferroni correction will be applied.

The sample size is small, but was determined by specifying a 95% CI with a relative width of 30% for the duration of action (12). However, as previous studies have used lower total insulin dosages and studied patients for maximal 24 hours, a very meaningful sample size calculation cannot be performed.

1ml of additional serum and plasma will be stored for batch analysis of cytokines and not yet defined parameters (not part of this protocol)

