Previous studies demonstrated both a delayed and a sustained blood glucose-lowering effect with insulin detemir and insulin glargine compared with conventional NPH insulin in healthy subjects (9-11). These results also revealed that a higher molar dose of insulin detemir was needed to achieve comparable glycemic control similar to that observed with NPH insulin (10). Importantly, glucose clamp studies and clinical trials have shown that the variability of the glucose lowering action of insulin detemir and glargine are reduced compared to NPH insulin in diabetic patients. In patients with type 1 diabetes, the mean duration of action of insulin detemir at clinically relevant insulin doses ranged between 12 to 23 hours, while the mean ( $\pm$  SE) duration of action of glargine was  $22 \pm 4$  hours (12, 13). The pharmacokinetics and pharmacodynamics of s.c. injected insulin are dose-dependent. Thus, both the peak and the duration of action were prolonged after injecting increasing doses of regular insulin, rapidly acting insulin analogues or NPH-insulin (14). One study with insulin detemir in patients with type 1 diabetes confirmed a dose-dependent increase in duration of action (12). This is important, as the dosage requirements in type 2 diabetes can be very high, especially in obese subjects with marked insulin resistance. Yki-Järvinen et al reported daily injected doses of up to 168 Units of basal insulin per day (15).

In clinical practice further weight gain with insulin therapy in obese patients with type 2 diabetes is a major barrier to insulin therapy. Interestingly, studies with insulin detemir have shown significantly less weight gain compared to NPH insulin (16). Research concerning the potential mechanisms for this weight-neutral behavior of detemir is ongoing.

In obese patients, doses of up to 1.5-2 U/kg body weight of basal insulin are increasingly used. However, most previous pharmacodynamic studies used lower doses of insulin detemir (0.6 U/kg body weight) (9, 10, 17) or insulin glargine (18-21) and investigated either lean or slightly overweight patients (9, 10, 12, 13, 17-21), but not patients with frank obesity. Thus, pharmacodynamic parameters (maximum action; duration of action) of moderate to high doses of subcutaneously applied detemir and glargine insulin, which are increasingly used in severely obese subjects, have not been reported up to date.

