### 1. Primary endpoint:

#### ○ Pharmacodynamics:

- The glucose consumption over time to maintain euglycemia: i.e. the peak of action, the time from peak to half maximal action, the total duration of action will be assessed following a single subcutaneous injection of two different doses of insulin detemir and glargine.
- The total duration of action is defined as the time between the beginning of action (from the time of 50% reduction in intravenous insulin infusion) until the end of action when plasma glucose consistently exceeds 8.3 mmol/l after the glucose infusion had been stopped, or after 36 h, whichever comes first (12, 13) of both doses and of both insulins.
- If the glucose-insulin-lowering effects of the 2 insulins are not equal at identical insulin dosages, the pharmacodynamics will be compared at the same effect level (standardized activity ratio, see below).

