### 3.2.1. Inclusion criteria:

- History of type 2 diabetes mellitus treated with insulin and/or metformin, and/or sulfonylureas
- Age 18-65 years
- Body mass index > 35 kg/m^2
- HbA1c >6.0% and < 10%

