### 3.3.2. Inpatient metabolic studies

Patients eligible to participate in the study based on the results of the screening visit will be admitted to the Department of Medicine, University Hospital Basel ([name]) at 7 am after fasting overnight for approximately 40 h, including an overnight stay. In patients on sulfonylureas these will be discontinued for 4 weeks before beginning the study and be withheld during the total duration of the study. Metformin will be paused 48 h (kinetic wash-out) and long-acting basal insulins will be paused 48-72 h prior to the study. If necessary, short-acting insulin will be given up to the evening prior to the study to keep blood glucose levels below 10 mmol/l.

An intravenous cannula will be inserted into an antecubital vein for the infusion of insulin and glucose. A second intravenous canula will be placed in a dorsal hand vein to obtain frequent blood samples for measurement of plasma glucose concentration.

At the beginning of the study a variable intravenous infusion of human soluble insulin will be started at 8 am to reach euglycemia at a plasma glucose level of 5.5 mmol/l within 30-60 minutes. At 10 am a single subcutaneous injection of either insulin detemir or insulin glargine will be administered in the thigh in two different dosages (0.8 and 1.6 IU/kg body weight) in randomized order. Intravenous regular insulin will be tapered when plasma glucose falls below 5.5 mmol/l.

Plasma glucose will be monitored at frequent intervals every 10 to 30 min (goal: plasma glucose 5.5 mmol/l; total blood needed 2 ml/measurement), and glucose 10% will be

administered by continuous i.v. infusion (syringe pump) using an algorithm to maintain plasma glucose levels at 5.5 mmol/l. Blood will also be drawn every 2 h for the first 6 h and subsequently every 6 h for the measurements of the serum concentrations of C-peptide, insulin detemir and insulin glargine using specific radioimmunoassays.

Each subject will be studied at four occasions in order to study the effects of two different doses (0.8 and 1.6 IU/kg body weight) of insulin detemir and of insulin glargine,, respectively. The procedures will be identical during each study. The time period between the different studieis always at least 7 days.

Each inpatient metabolic study will last 36 hours after the injection of insulin detemir or until the plasma glucose will consistently increase to > 8.3 mmol/l in the absence of glucose infusion.

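### End of action, which fixes the duration-of-action primary endpoint, has two wordings that part at the edges, and sessions reaching 36 h are scored as completed durations

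*Protocol*

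**What the plan says.** End of action appears in three places in the protocol.

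- **Section 2, primary endpoint.** Duration starts at the halving of the i.v. insulin rate ("from the time of 50% reduction in intravenous insulin infusion") and ends "when plasma glucose consistently exceeds 8.3 mmol/l after the glucose infusion had been stopped, or after 36 h, whichever comes first". References 12 and 13 are cited for this.
- **Section 3.3.2, trial schedule.** The inpatient study lasts 36 h after the injection, or "until the plasma glucose will consistently increase to > 8.3 mmol/l in the absence of glucose infusion".
- **Section 3.5.3, calculations.** Action ends when "plasma glucose consistently increases to > 8.3 mmol/l despite adaptation of glucose infusion". This sentence neither requires the infusion to be off nor mentions 36 h.

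Duration of action is named in the primary null hypothesis (Section 3.5.1), is an outcome of the mixed model with a random subject effect, and is the basis of the sample size (both Section 3.5.3). Section 3.5.2 also sets its mean against 30 h.

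The rationale ties references 12 and 13 to a different population: "In patients with type 1 diabetes, the mean duration of action of insulin detemir" and that of glargine are quoted from them. Section 3.2.1 admits type 2 patients on insulin, metformin or sulfonylureas in any combination, with "HbA1c >6.0% and < 10" percent. They do not eat during the session.

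The clamp target is 5.5 mmol/l in Section 3.3.2 and 5 mmol/l in Section 3.5.3.

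**The concern.** A primary endpoint needs one rule that gives one value per session. Here the section that defines the endpoint and the section that says how to calculate it differ on two elements: the state of the infusion and the time limit. Two analysts, each following one section, could derive different durations from the same clamp record, or one could derive none.

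The second part concerns the cap. Section 2 makes 36 h an end of action in its own right, so a session in which glucose never passed 8.3 mmol/l enters the mixed model as if the end had been observed. The threshold comes from studies that the protocol describes as type 1. A fasting type 2 patient with some insulin secretion could settle between 5.5 and 8.3 mmol/l and run to the cap. The cap is also reached if a high dose really acts beyond 36 h.

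At stake are the contrasts between insulins and between doses, which a ceiling compresses, and the comparison of the mean with 30 h, which lies only 6 h below the cap.

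**Working it through.** **1. The definitions compared.**

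| Situation | Section 2 (and the stopping rule in 3.3.2) | Section 3.5.3 |
|---|---|---|
| Above 8.3 mmol/l, infusion off, before 36 h | End at crossing | End at crossing |
| Above 8.3 mmol/l, infusion still running | Not yet an end | End at crossing |
| 8.3 mmol/l not passed by 36 h | End at the cap | No value |

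The first row should be the usual one. The infusion algorithm aims at 5.5 mmol/l, so adapting it as glucose rises normally means turning it down to zero before 8.3 mmol/l is passed for good. The rules differ in the other two rows.

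**2. The plan's own figure.** Twelve subjects are justified by a 95% CI of relative width 30% for duration. No SD is given, so 12 can be neither reproduced nor refuted. Working backwards, with 30% as full width and t(0.975, 11) = 2.201, the implied coefficient of variation (CV) is 0.15 × √12 / 2.201 = 23.6%. It serves below only as one plausible spread.

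**3. Effect of scoring 36 h as an observed end.** Assume normal durations with mean m and SD s = CV × m, and let a = (36 − m)/s. The mean of the capped values is

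m·Φ(a) − s·φ(a) + 36·(1 − Φ(a)).

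Two CVs are used: 4/22 = 18.2% and the 23.6% above. The first treats the ± 4 h around 22 h for glargine (Section 1) as an SD. The protocol labels it an SE, so this is an assumption. For simplicity the cap is set at 36 h on the duration scale. Duration starts at the cut in i.v. insulin while Section 3.3.2 counts 36 h from injection, so the effective cap is 36 h less the onset time.

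Example, CV 18.2%, m = 32: s = 5.82, a = 0.6875, Φ = 0.754, φ = 0.315. The capped mean is 32 × 0.754 − 5.82 × 0.315 + 36 × 0.246 ≈ 31.15 h. For m = 24 it is 24.00 h. The difference is 7.15 h instead of 8 h.

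| True means (h) | True difference (h) | Observed, CV 18.2% (share of longer arm at cap) | Observed, CV 23.6% (share of longer arm at cap) |
|---|---|---|---|
| 22 and 28 | 6 | 5.87 (6%) | 5.64 (11%) |
| 24 and 32 | 8 | 7.15 (25%) | 6.61 (30%) |
| 26 and 36 | 10 | 7.42 (50%) | 6.74 (50%) |
| 28 and 40 | 12 | 6.80 (71%) | 6.26 (66%) |

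The loss is small while durations stay well under the cap and large once the longer arm approaches it.

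**4. Patients who never cross in any session.** If a share q of patients does so, a true difference of 6 h becomes about 6 × (1 − q): 5.4 h at q = 0.10, 4.5 h at 0.25, 3.0 h at 0.50. It is approximate because capped sessions can still differ through onset. The documents give no value for q.

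**5. The 30 h comparison.** If 3 of 12 patients score 36 h and the other 9 average 28 h, the mean is (3 × 36 + 9 × 28)/12 = 360/12 = 30 h. The cap alone then moves the mean from 28 h to the tested value. If action truly outlasts 36 h, the cap instead pulls the mean down. The split of 3 and 9 is an assumption.

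**The case against.** **The wordings say the same thing.** Adapting an infusion that targets 5.5 mmol/l means reducing it, so it would be off before 8.3 mmol/l is consistently passed, and Section 2 already settles the session that never gets there. Most of this stands: calling the definitions incompatible would overstate it. But Section 3.5.3 does not require the infusion to be off and does not carry the cap, and it is the section an analyst would work from.

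**Non-crossing is conjecture.** HbA1c just above 6.0% is a value on treatment. Section 3.3.2 then stops sulfonylureas for 4 weeks, metformin for 48 h and basal insulin for 48–72 h, foresees short-acting insulin to hold glucose below 10 mmol/l, and starts i.v. insulin to bring it to 5.5 mmol/l. The design expects many subjects to need insulin. This also stands as far as frequency goes. A reader might infer that in mild patients the endpoint measures their own secretion and the fast instead of the injected insulin. The documents do not support that: measuring C-peptide does not show how much is secreted, and no rate of non-crossing is given.

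**A delay in crossing is no bias.** A lag similar across a subject's four sessions cancels from within-subject contrasts. That is right for sessions that cross. It does not help when some reach the cap and others do not.

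**Handling of capped values belongs in the SAP.** Silence would be no finding. Here the protocol is not silent: Section 2 makes 36 h an end of action, and Section 3.5.3 names the model that receives the value.

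**An end defined by the glucose infusion rate would be better.** This might be inferred, but as a replacement primary endpoint it is a debatable trade. It gives no sensible duration if a session needs no glucose, it is still affected by endogenous insulin, and it depends on a clamp target that the protocol states in two ways.

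**Conclusion.** The point holds in a limited form. The discrepancy between Section 3.5.3 and Sections 2 and 3.3.2 is documented and affects a variable in the primary null hypothesis, the main model and the sample-size basis. In ordinary sessions it changes nothing. It matters when glucose is above 8.3 mmol/l with the infusion running, and when 36 h is reached without a crossing.

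Scoring 36 h as an observed end can shrink the contrasts between insulins and doses and can shift the mean compared with 30 h in either direction. In the illustrations the loss runs from 0.13 h of a 6 h difference (5.87 observed) to 5.74 h of a 12 h difference (6.26 observed). These sizes rest on assumed normal durations, assumed CVs and assumed true means, and the effect of patients who never cross rests on an assumed share. The protocol supports only that such sessions are plausible.

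Total glucose consumption, the other quantity in the primary null hypothesis, is not measured by the 8.3 mmol/l threshold, so this point concerns duration of action.

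**What to change.** - State one end-of-action definition for the endpoint and use it in Sections 2, 3.3.2 and 3.5.3. It should include the infusion condition, the 36 h limit and whether that limit runs from the injection or from the start of action.
- Reconcile the clamp target in Sections 3.3.2 and 3.5.3. Which target applies and when a session stops are for the sponsor to settle.
- Treat sessions that have not met the definition by 36 h as right-censored, for example in a censored-normal model with a random subject effect, instead of as observed ends at 36 h.
- Report the number of such sessions by insulin and dose.
- Optionally, add an end of action based on the glucose infusion rate as a sensitivity analysis, not as a replacement primary endpoint.

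Censoring stops capped sessions from being averaged in as near-zero differences. It does not separate injected from endogenous insulin, so the count and the sensitivity analysis are needed to interpret the mean against 30 h.

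The cost is a wording change and slightly more analysis work on data already recorded, with wider intervals where sessions are censored.

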### 3.2. Trial population:

Twelve morbidly obese subjects with type 2 diabetes (BMI >35 kg/m^2) will be recruited from the outpatient clinic of the Division of Endocrinology, Diabetes and Clinical Nutrition at the University Hospital Basel.

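### The primary tests use single-step Bonferroni, which is valid but needlessly conservative with 12 patients; Holm's step-down would give the same error control and never reject less

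*Protocol*

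**What the plan says.** Section 3.5.3 of the protocol states: "As there are several primary endpoints, a Bonferroni correction will be applied". It names neither a divisor nor a sequential procedure.

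The primary null hypothesis in section 3.5.1 is: "The total glucose consumption and the mean duration of action will not be different between the two insulins and the two insulin dosages". Read as main effects, that is two outcomes by two contrasts. Section 2 also lists, under the primary endpoint, "i.e. the peak of action, the time from peak to half maximal action, the total duration of action will be assessed", so the set of primary outcomes is not the same in the two places.

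The trial population is "Twelve morbidly obese subjects with type 2 diabetes" (section 3.2), and "Each subject will be studied at four occasions" (section 3.3.2), once for each combination of insulin and dose. Section 3.5.3 admits that the sample is small. It bases the number on the precision of a confidence interval for duration, not on power.

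On dose, section 6 argues from the premise "As all insulins show a dose-dependent prolongation of their action profile". On the insulins, section 3.5.3 treats their unit-for-unit equivalence as disputed.

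**The concern.** Single-step Bonferroni holds every test at alpha/m, whatever happens to the others. If the dose contrasts belong to the family and are rejected, their share of alpha stays locked up and the insulin contrasts are still judged at alpha/m. A step-down procedure releases that share.

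With 12 patients and no power calculation, a test level stricter than error control requires makes it more likely that a real difference between the insulins is missed. Recovering that power needs no further patient, clamp session or blood sample.

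**Working it through.** **The plan's own figure.** The sample size rests on a 95% interval with 30% relative width, but no coefficient of variation (CV) is given, so it cannot be reproduced. Taking 30% as the full width, 2 × t(0.975, 11 df) × CV/√12 = 0.30 gives CV = 0.30 × 3.464/(2 × 2.201) = 23.6%. The point here does not depend on this.

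**Why Holm never rejects less.** Order the p-values and compare the k-th smallest with alpha/(m − k + 1), stopping at the first failure. Each of these levels is at least alpha/m, so any p-value that Bonferroni rejects is also rejected by Holm. Strong family-wise control holds under any dependence.

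**Inputs from the protocol.** 12 patients and 4 sessions each, giving 48 observations. Four tests, inferred from section 3.5.1.

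**Assumptions.** Two-sided family-wise 5%. Correlation of 0.5 between the outcomes. Error df of 48 − 12 (patients) − 3 (treatments) − 3 (periods) = 30. Effects expressed in within-patient SDs.

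**Levels.** Bonferroni: 0.05/4 = 0.0125 for every test. Holm: 0.0125, 0.0167, 0.025 and 0.05 in order. Once both dose contrasts are rejected, the smaller insulin p-value is tested at 0.025 and, if rejected, the last at 0.05.

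**Standard error.** Each main effect compares 24 with 24 observations, so SE = SD × √(2/24) = 0.289 SD. An insulin effect of 0.8 SD gives a noncentrality of 0.8/0.289 = 2.77. Against the critical t of 2.657 (0.0125 two-sided, 30 df), power is 55%. That is the Bonferroni figure.

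**Simulated power for one insulin contrast of 0.8 SD:**

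| Family | Dose effect | Insulins differ on | Bonferroni | Holm | Gain (points) |
|---|---|---|---|---|---|
| 4 tests | 1.5 SD | both outcomes | 55.4% | 72.1% | 17 |
| 4 tests | 1.0 SD | both outcomes | 55.4% | 69.4% | 14 |
| 4 tests | 0.5 SD | both outcomes | 55.4% | 60.6% | 5 |
| 4 tests | 1.5 SD | one outcome | 55.4% | 66.3% | 11 |
| 4 tests | 1.0 SD | one outcome | 55.4% | 64.0% | 9 |
| 4 tests | 0.5 SD | one outcome | 55.4% | 57.3% | 2 |
| 2 outcomes only | not in family | both outcomes | 66.1% | 72.0% | 6 |
| 2 outcomes only | not in family | one outcome | 66.1% | 66.2% | 0 |

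A mixed case, with a dose effect of 1.5 SD on consumption but 0.5 SD on duration (33 df, no period term), gives 56% to 66% when both outcomes differ by insulin. The gain is 6 points when only one does.

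**Error rate.** With dose effects of 1.5 SD and no insulin difference, the chance of any false insulin claim is about 2.4% under Bonferroni and 4.7% under Holm. Both are within 5%.

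**The case against.** Four objections carry weight.

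- **Bonferroni is not an error.** It controls the family-wise rate, and choosing another valid method is a matter of efficiency. This stands. The exact divisor could also be left to an analysis plan. The choice of a plain Bonferroni correction, however, is made in the protocol itself.
- **The family of four is inferred.** Section 3.5.3 ties the correction to the number of endpoints, not of contrasts. If alpha is divided only over the two outcomes, the dose contrasts hold no share of it and most of the gain disappears. This is a fair reading.
- **The dose effects are not certain to be rejected.** A reader might infer from section 6 that they are a foregone conclusion and that the insulin comparison is the only open question. The protocol does not support that. Section 1 cites a single dose-response confirmation for detemir, in type 1 diabetes, and says that data at moderate to high doses in severely obese patients are lacking. Section 2 makes the dose-response relationship the primary aim. It also ends the measurement of duration at 36 h, which could blunt the dose contrast on that outcome.
- **Intervals.** The sample was justified by interval precision, and Bonferroni has matching simultaneous intervals. Holm has none as simple, so an unadjusted interval may exclude zero where Holm does not reject, and a Bonferroni interval may include zero where it does. This cost is real but modest.

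None of these gives a case in which Holm rejects less than Bonferroni.

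**Conclusion.** The point holds as an efficiency improvement. Single-step Bonferroni is valid but stricter than it needs to be, and Holm gives the same family-wise control with no added assumption.

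For an insulin effect of 0.8 SD with four tests, the gain is about 5 to 17 points when both outcomes differ by insulin and about 2 to 11 when one does, over dose effects of 0.5 to 1.5 SD. With alpha split over the two outcomes only, it is about 0 to 6 points. All of this rests on assumed effects, correlation and degrees of freedom.

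A reader might take the most favourable case as the expected benefit: with a dose effect of 1.5 SD, power to show the insulin difference on both outcomes goes from 38% to 63%. The documents give no effect size or SD to support that. At a dose effect of 0.5 SD the same power goes only from 38% to 47%. Nor should the point be read as a type I error fault, for there is none.

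**What to change.** Replace the Bonferroni sentence in section 3.5.3 by: *The primary tests are the insulin and dose main effects on total glucose consumption and on duration of action (four tests), tested by the Holm step-down procedure at a two-sided family-wise 5%.* Then add which intervals will be reported: Bonferroni simultaneous intervals, or 95% intervals clearly labelled as unadjusted.

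Naming the family is part of the fix, because the protocol has no single list of primary tests. Section 2 should be brought into line by stating that peak of action and time from peak to half-maximal action lie outside this family. If they are to stay primary, the list becomes longer and Holm applies to it in the same way.

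The change costs one or two sentences, made before any data are seen. Its downside is the occasional mismatch between a Holm decision and the reported interval, which the text should acknowledge.
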